### Statistical analysis

The trial has two co-primary outcomes, heat-related illness and quality of life. These outcomes will be evaluated independently to assess the effectiveness of the intervention. All statistical analyses will be conducted using STATA 18.0 (https://www.stata.com), following an intention-to-treat approach while accounting for the cluster-randomised trial design. Baseline characteristics will be analysed to assess comparability between intervention and control arms. Descriptive statistics will summarise household and participant characteristics, and any important imbalances at baseline will be adjusted for in the analysis. No interim analysis or formal stopping guidelines are planned given the low-risk nature of the intervention.

Statistical analyses will account for the cluster-randomised design by incorporating clustering through random effects or robust variance estimators, as appropriate. For outcomes measured repeatedly over time, within-participant correlation will be accommodated using repeated-measures mixed-effects models. Intervention assignment and seasonal variation will be included as fixed effects in all applicable models, while relevant baseline covariates and baseline outcome values (where available) will be adjusted for. Model assumptions, including overdispersion for count outcomes, will be assessed and alternative modelling approaches (eg, negative binomial models) will be used where appropriate. Missing data will be examined and handled using complete-case analyses or multiple imputations, depending on the extent and pattern of missingness. Sensitivity analyses will be performed to assess the robustness of findings to different assumptions regarding missing data.

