### Sample size

Sample sizes were calculated for both the primary outcomes to provide at least 80% power at the 5% significance level. Based on heat-related symptoms and illness prevalence of 28.9%^29^ and an estimated intra-cluster correlation coefficient (ICC) of 0.0122, we calculate that 11 clusters per arm (22 clusters in total) with 70–80 households per cluster are needed to detect a 30% relative difference in heat-related illnesses while allowing for a 10% attrition rate. We treat 28.9% as a conservative estimate given the longitudinal nature of the primary outcome, as cumulative incidence over the surveillance period is expected to exceed this single-timepoint prevalence. To assess quality of life changes, we estimate that with 11 clusters per arm, 60 households per cluster are required based on the variability in baseline WHOQOL-BREF scores reported,^30^ which documented an average score of 68 (18.0) to detect a difference of 4 points in quality of life score, assuming an ICC of 0.015. As the heat-related illness outcome required the larger sample size, the final enrolment target was set at 70–80 households per cluster, which also provides adequate power for the quality-of-life outcome. To assess physiological heat strain, we calculated that a sub-sample of eight adults (aged 18 years–60 years) per cluster (balanced by gender) would be required to detect a 15% change in average heart rate among those who are exposed to heat stress, assuming a baseline of 66±12 bpm,^31^ an ICC of 0.1736 and 90% power. Given the complexity of the assessment process, we anticipate a higher attrition rate in this subset and have inflated the sample size by 30% to 10 individuals.

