For binary outcomes, the ICC was derived from an assumed cluster-level prevalence variation of ±10%, with the coefficient of variation (CV) estimated from this range and the ICC subsequently calculated using the relationship ICC=k² × P/(1−P), where k is the assumed between-cluster CV of the prevalence, following Pagel *et al*.^32^ For continuous outcomes, the ICC was estimated as the ratio of between-cluster variance to total variance,^33^ with total variance sourced from reference studies and a minimum between-cluster difference of ±9 units assumed. Each co-primary outcome is independently powered at 80% or above. To control the family-wise type I error rate across the two co-primary outcomes, hypotheses will be tested using a pre-specified fixed-sequence (hierarchical) procedure: heat-related illness will be tested first at the two-sided 0.05 level, and quality of life will be tested at 0.05 only if the first test is significant. As each outcome is independently powered, this procedure incurs no loss of power. Quality of life is assessed at three time points per year over 2 years; the cross-sectional calculation above is therefore conservative, as the planned repeated-measures mixed-effects analysis increases precision by combining information across visits.

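### The Statistical analysis section says the co-primary outcomes are evaluated independently, which read literally conflicts with the fixed testing sequence in the Sample size section

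*Protocol article*

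**What the plan says.** The Sample size section gives the testing rule, and its purpose is stated as: "To control the family-wise type I error rate across the two co-primary outcomes". In the first step, "heat-related illness will be tested first at the two-sided 0.05 level". The second step depends on the outcome of the first: "quality of life will be tested at 0.05 only if the first test is significant". The section adds that "Each co-primary outcome is independently powered at 80% or above" and concludes from this that the sequence costs no power.

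The Statistical analysis section opens with "The trial has two co-primary outcomes, heat-related illness and quality of life" and continues "These outcomes will be evaluated independently to assess the effectiveness of the intervention". It states no significance level for these tests, no order of testing and no rule for declaring success. The Primary outcome analysis subsection then describes a Poisson model giving incidence rate ratios for heat-related illness, and adjusted mean differences for quality of life, each with 95% confidence intervals. Neither place mentions the sequence or refers back to the Sample size section.

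**The concern.** Under a fixed sequence, the confirmatory status of quality of life depends on the heat-illness result. A sentence saying that the outcomes are evaluated independently to judge effectiveness points the other way. The Objective section lists heat-related health risk and quality of life as two primary aims without ranking them, so it does not settle the matter.

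What is at stake is the split result: heat-related illness not significant, quality of life with p<0.05. One analyst, following the Sample size section, would report quality of life without a confirmatory claim. Another, working from the Statistical analysis section alone, could declare a positive co-primary outcome. If the reading is chosen after the results are seen, the prespecification that the Sample size section relies on is lost.

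**Working it through.** **Inputs.** From the Sample size section: two-sided 0.05 for heat-related illness; 0.05 for quality of life, conditional on the first (taken as two-sided too); at least 80% power for each; 28.9% prevalence, 30% relative reduction (to 0.7 × 28.9% = 20.23%), ICC 0.0122, 10% attrition; SD 18.0, difference 4, ICC 0.015, 60 households per cluster; 11 clusters per arm. The correlation between the two test statistics is not given, so a range is assumed.

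**1. The plan's own sample sizes (two-sided 0.05, 80% power).**
- Heat-related illness: n = [1.96·√(2p̄(1−p̄)) + 0.8416·√(p₁(1−p₁) + p₂(1−p₂))]² / (p₁−p₂)², with p₁ = 0.289, p₂ = 0.2023 and p̄ = 0.24565, gives 386 per arm. With 72 analysed per cluster, the design effect is 1 + 71 × 0.0122 = 1.8662, and 386 × 1.8662 / 72 = 10.0 clusters. One more as a small-sample allowance gives 11. Attrition: 72 / 0.9 = 80 households.
- Quality of life: n = 2(1.96 + 0.8416)² × 18² / 4² = 318 per arm. The design effect is 1 + 59 × 0.015 = 1.885, and 318 × 1.885 / 60 = 9.99 clusters. One more gives 11.

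Both stated sizes reproduce. Each is the size for that outcome tested alone at the full 0.05. Neither takes account of the sequence.

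**2. Family-wise error under the fixed sequence.** If neither outcome is affected, no claim can be made unless the first test rejects, so the error is 0.05. If only heat-related illness is affected, a false quality-of-life claim needs both tests to reject, so its probability is at most 0.05.

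**3. Family-wise error if both outcomes were tested unconditionally, with success on either.** For uncorrelated tests it is 1 − 0.95² = 0.0975. For correlated tests (bivariate normal):

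| Correlation | Error |
|---|---|
| 0 | 0.0975 |
| 0.3 | 0.095 |
| 0.5 | 0.091 |
| 0.7 | 0.083 |
| 0.8 | 0.078 |
| 0.9 | 0.070 |

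**4. How often the two readings would part.** This is P(heat-related illness not significant and quality of life significant):
- neither affected: 0.95 × 0.05 = 0.048 uncorrelated, 0.041 at correlation 0.5;
- both affected, 80% power each: 0.20 × 0.80 = 0.16 uncorrelated, 0.113 at correlation 0.5;
- only quality of life affected, 80% power: 0.95 × 0.80 = 0.76 uncorrelated, about 0.77 at correlation 0.5.

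**5. Power for quality of life under the sequence.** Both tests must reject. With 80% power each, this is 0.80 × 0.80 = 0.64 uncorrelated, 0.67 at correlation 0.3 and 0.69 at correlation 0.5. If 70 households per cluster were analysed for both outcomes, the separate powers by normal approximation would be 0.831 and 0.864, and 0.831 × 0.864 = 0.72 uncorrelated, still below 80%.

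**The case against.** A reader might infer that the trial has two competing decision rules, one with a false-positive rate of 9–10%. The document does not support that. The Sample size section contains the only complete rule, with aim, order, level and condition, and that rule holds the error at 5%. The Statistical analysis section sets no level and nowhere says that either outcome suffices.

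The word *independently* can also mean one model per outcome with no composite, which is what the Primary outcome analysis subsection describes. The authors use the same word for power directly beside the fixed sequence, so they evidently saw no clash. Nor is a condensed article obliged to state the sequence twice.

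A reader might further infer that the split result is especially likely because the trial is unblinded and quality of life is self-reported. Heat-related illness also rests largely on symptoms collected at household visits by unblinded staff, so lack of blinding gives no clear reason for quality of life alone to move.

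These objections stand, and they reduce the point to a conflict of wording. They do not remove it. The sentence concerns how effectiveness is judged, and read as written it gives a different answer from the Sample size section on a co-primary outcome.

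On power, the authors' statement is right in one sense: a fixed sequence needs no split of alpha, and heat-related illness loses nothing. It is not right for quality of life.

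**Conclusion.** The point holds as an inconsistency to reconcile. It does not show that multiplicity control is absent. Taken literally, the two sections allow opposite confirmatory conclusions when only quality of life is significant. The error of about 9–10% applies only if the analysis section is read as two unconditional two-sided 0.05 tests with success on either, and only at correlations from 0 to 0.5. It falls to about 7–8% at correlations of 0.8 to 0.9. The disagreement probabilities in step 4 likewise assume an analyst who does not apply the sequence.

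One related statement is wrong whichever reading is taken. Under the sequence, the chance of a confirmatory quality-of-life result is about 64–69% when each outcome has 80% power and the correlation is 0 to 0.5. The loss would vanish only if the tests were perfectly correlated or power for heat-related illness were close to 100%.

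**What to change.** In the Statistical analysis section, replace the sentence on independent evaluation with wording such as: *Each co-primary outcome is analysed in its own model. Confirmatory conclusions follow the fixed sequence given under Sample size: heat-related illness at two-sided 0.05, then quality of life at two-sided 0.05 only if heat-related illness is significant. If it is not, the quality-of-life estimate and 95% CI are reported without a confirmatory claim.*

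In the Sample size section, replace the statement that the procedure costs no power. Say that heat-related illness keeps its full power, that the 80% for quality of life is its power when tested alone, and that the chance of a confirmatory quality-of-life result under the sequence is lower (about 64–69% on the assumptions above).

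The cost is two sentences, made before any results by arm are seen. The design, the sample size and the sponsor's chosen procedure stay as they are. The downside is that quality of life cannot be claimed on its own. The fixed sequence already implies this, and the corrected power statement would make it visible.

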#### Primary outcome analysis

For each participant, a summary record will be constructed comprising the number of heat-related illness episodes and the number of assessment occasions (or person-time) over which the individual was observed. To assess the intervention effect, a Poisson regression model with cluster-level random intercepts will be used, accounting for intra-cluster correlation. The number of heat-related illness episodes/events will serve as the numerator, while person-weeks at risk will be used as the denominator. Results will be presented as incidence rate ratios (IRRs) with 95% CIs.

Duplicate reports identified across multiple sources will be flagged in the database using participant ID, household ID, date of onset, symptoms and care-seeking information to ensure that each event is counted only once. Symptoms or events continuing from a previous reporting period will be considered part of the same illness episode. A new episode will be defined as either the onset of symptoms following a symptom-free interval of at least two days after the previous episode or the occurrence of additional new symptoms in a participant with ongoing previously reported symptoms. For quality-of-life assessments, the mean increase from year 1 to year 2 would be compared three times a year. Summer and winter quality of life means would be segregated and compared. Results will be reported as adjusted mean differences with 95% CIs.

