### Cluster randomisation

We will employ a constrained randomisation procedure as described by Lock, Morgan and Rubin (2012),^36^ rather than relying on a single random allocation, the randomisation process will be implemented using the Stata ‘randomise’ command, which generates multiple allocation schemes in the background and evaluates balance across prespecified baseline covariates. An allocation achieving an acceptable level of balance between study arms at the cluster level will then be selected for the trial. Geographically designed clusters will be randomly assigned by an independent statistician to either the intervention arm, receiving the Heat Adaptation Bundle (ReHAB) or the control arm. Each random allocation is evaluated for covariate balance on three pre-specified characteristics: population residential density, household structural type (single-storey vs double-storey) and roof type (permanent, semi-permanent or natural materials).

Additionally, simple randomisation would be used to select eight households for the in-depth assessment from a subset in both intervention and control groups. Within these selected households, the Kish grid method would be used to randomly select the eligible adult if more than one adult is present. If the indexed participant refuses, the next eligible adult will be considered from the same household. If all eligible adults from a household refuse to participate, then another household will be included. Male and female participants for the subset will be selected systematically.

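### Covariates are chosen by observed imbalance and never tied to the three variables that constrain allocation, and no small-sample method is stated for 22 clusters

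*Protocol article*

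**What the plan says.** Cluster randomisation: allocation is by constrained randomisation. "Each random allocation is evaluated for covariate balance on three pre-specified characteristics": residential density, single- versus double-storey structure, and roof type.

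Statistical analysis: clustering is handled by "incorporating clustering through random effects or robust variance estimators, as appropriate". The first covariate rule is that "any important imbalances at baseline will be adjusted for in the analysis". A later sentence in the same section also allows adjustment for baseline covariates considered relevant, without listing them, and for the baseline value of the outcome where there is one.

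Primary outcome analysis: for illness episodes per person-week, "a Poisson regression model with cluster-level random intercepts will be used, accounting for intra-cluster correlation". The result is an incidence rate ratio with a 95% CI. Reference distribution, degrees of freedom and variance correction are not mentioned.

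Sample size: both co-primary outcomes are sized "to provide at least 80% power at the 5% significance level". In the fixed sequence, "heat-related illness will be tested first at the two-sided 0.05 level", and quality of life follows only if illness is significant.

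**The concern.** Two features of the analysis text fit the design poorly.

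- **Covariates.** An analysis of a constrained design should condition on the variables that constrained it. Constrained allocation makes those variables look alike in the two arms, so a rule that waits for imbalance will tend to pass over them and select others after the data are seen. If they predict the outcome, the unadjusted standard error still carries variation that the allocation has already balanced away, and the test is conservative.
- **Number of clusters.** The treatment effect is estimated between 22 clusters. Usual software output for a Poisson random-intercept model is a maximum-likelihood variance referred to the normal distribution. With 11 clusters per arm, that is liberal.

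Illness is the gatekeeper of the fixed sequence, so family-wise error control depends on this test holding its level. The open covariate rule also lets the analyst choose among models that differ in level.

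**Working it through.** **1. The plan's own figure.** Inputs from Sample size: "heat-related symptoms and illness prevalence of 28.9" per cent, "an estimated intra-cluster correlation coefficient (ICC) of 0.0122", a 30% relative reduction (28.9% to 20.23%), 11 clusters per arm and 10% attrition.

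- ICC: reading the stated ±10% spread as ±10 percentage points = ±2 SD (an assumption), k = 0.05/0.289 = 0.173. Then k²P/(1−P) = 0.0299 × 0.289/0.711 = 0.0122, which agrees with the plan.
- Individually randomised n per arm: 386 (409 with continuity correction).
- Cluster size: m = n(1−ICC)/(11 − n·ICC) = 386 × 0.9878/(11 − 4.709) = 60.6, and 60.6/0.9 = 67.3. With 409: 67.2, and 74.7 after attrition.

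The stated 70–80 households is reproduced by normal-based formulas.

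**2. Closed-form level of a nominal 5% z test, 22 clusters.** With p cluster-level covariates, residual df are ν = 20 − p. The true level is:

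- REML-type variance: P(|t_ν| > 1.96)
- Robust variance with the G/(G−1) factor: P(|t_ν| > 1.96·√(ν/21))
- ML variance: P(|t_ν| > 1.96·√(ν/22))

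| Covariates | ν | REML-type | Robust | ML |
|---|---|---|---|---|
| 0 | 20 | 6.4% | 7.0% | 7.6% |
| 3 | 17 | 6.7% | 9.6% | 10.3% |

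This step ignores the constrained allocation.

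**3. Simulated level under constrained allocation.** Poisson random-intercept model fitted by ML (Laplace), 4,000 null trials per scenario. Assumptions, none of them in the article beyond those noted: log-scale cluster SD 0.173 (taken from k), about 450 persons per cluster, 0.289 episodes per person (about 130 events per cluster), and allocation drawn from the best 10% of 200 on three covariates. The share of between-cluster variance explained by those covariates is not given, so it is varied.

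| Analysis, z reference | 0 | 30% | 60% |
|---|---|---|---|
| Unadjusted | 8.0% | 4.6% | 2.6% |
| Adjusted for the three variables | 10.9% | 10.5% | 9.1% |
| Adjusted for imbalance-selected noise covariates (standardised difference above 0.5 among six; assumed) | 8.8% | 6.2% | 4.1% |

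Monte Carlo standard error at 5% is √(0.05 × 0.95/4000) = 0.34 points, so 4.6% cannot be told from 5%.

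Replacing z by t while keeping the ML variance is not enough. With non-prognostic covariates the level is 6.3% unadjusted (t, 20 df) and 8.2% adjusted (t, 17 df). The variance needs correcting too.

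**4. Cost in power of a t reference.** For illness at 70 households less 10%, m = 63:

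- Effective n per arm = 11 × 63/(1 + 62 × 0.0122) = 394.6
- SE = √[(0.289 × 0.711 + 0.2023 × 0.7977)/394.6] = 0.0305
- Noncentrality = 0.0867/0.0305 = 2.84

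Power before any covariate adjustment:

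| Analysed households per cluster | Illness, z | Illness, t (20 df) | Quality of life, t (20 df) |
|---|---|---|---|
| 63 (70 less 10%) | 80.9% | 77.2% | 80.8% |
| 72 (80 less 10%) | 83.6% | 80.1% | 83.3% |

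The quality-of-life column uses the plan's 4 points, SD 18 and ICC 0.015.

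**The case against.** The strongest reply is that much of this is read from silence. The article names a model, not a reference distribution. A degrees-of-freedom correction is the kind of detail a condensed article leaves to a fuller plan, which is not shown. That stands: a reader might infer that the trial will use uncorrected normal-based tests, but the text does not say so, and the silence alone would not be a finding.

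Second, a reader might infer that the three variables are excluded from the analysis. They are not. All three are baseline covariates and could be among those judged relevant. That also stands, but an unlisted set gives no assurance that they will be included.

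Third, the two effects oppose each other, and at a 30% explained share the unadjusted level is close to nominal. This rules out a flat claim that the 5% level fails. It does not rescue the plan, because the balance depends on a share nobody has stated.

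On power, the article calls 28.9% conservative because cumulative incidence should be higher. That is fair, and the shortfall at the lower end is small.

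What no reply removes is that the imbalance rule is stated and does not suit the constrained design.

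**Conclusion.** The point holds in limited form. The stated imbalance rule works against the constrained allocation, the three variables are not tied to the analysis, and the named illness model needs a small-sample method that the article does not give.

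Under default normal-based inference, the level of a nominal 5% illness test is uncertain: about 2.6% to 8.0% unadjusted across the assumed 0 to 60% range, and about 9% to 11% if the three variables are added with no correction. It would be tempting to conclude that the p values and intervals are wrong. The documents do not support that, because default inference is not stated and the direction of the net error is unknown.

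The figures rest on the simulation assumptions above and on a cluster SD derived from the plan's ICC. Quality of life was not simulated. The same reasoning applies to it, but no size is claimed.

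**What to change.** For both co-primary outcomes:

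- Replace the imbalance rule with prespecified adjustment for the three constraint variables and for the baseline outcome where available. State how each variable is coded at cluster level. If roof type needs two terms, there are four cluster-level covariates and ν = 16.
- Name one small-sample method per outcome that supplies both the p value and the 95% CI, so that they cannot disagree. For illness, this could be a covariate-adjusted cluster-level analysis of log rates with t on between-cluster df, or a randomisation test over the acceptable allocations with the CI found by inverting it. For quality of life, it could be REML with Kenward-Roger.
- Have the independent statistician save the set of acceptable allocations.
- Make both changes together, since adding the covariates alone raises the level.

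The cost is analysis wording and code; the three variables already have to be available for the randomisation. Intervals will be slightly wider. The statement of at least 80% power should be restated for the lower end of the enrolment range, where illness power on t with 20 df is about 77%. Power after covariate adjustment was not computed: it loses a few df and gains whatever between-cluster variance the covariates explain.

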### Data collection from subset population

Monthly data will be collected for in-depth understanding of heat stress and intervention effectiveness within the subset population (table 3). This will include thermal comfort, mental health and heat exposure assessment.

**Table 3 T3:** Schedule of outcome assessments and follow-up activities

Parameter	Time points	Details	Devices/Tools	Population/Unit
Primary outcomes				
All heat-related illness	Weekly during peak summers	Heat-related illnesses	Weekly community survey, health facility data, community surveillance	All members of included households
Quality of life	Mid of April, July and December for two consecutive years	Quality of life mean score	WHOQOL-BREF* questionnaire	Indexed adults of all included households
Secondary outcomes				
All-cause mortality	Weekly during peak summers	Any mortality occurring within the included clusters	Weekly community survey, health facility data, community surveillance	All members of included households
Hospital visit/hospitalisation	Weekly during peak summers	Any hospital admission or hospital visit occurring within the included clusters	Weekly community survey, health facility data, community surveillance	All members of included households
Indoor heat index	Continuous throughout the year	Indoor data loggers	iButton, Kestrel Drop D2, Temp-U	All included households
Thermal comfort (home)	Monthly	Self-reported comfort levels	Thermal comfort survey adapted from CHEQ-5†	Indexed adults randomised for sub-group
UTCI§	Continuous throughout summers	Outdoor only	Kestrel Drop D2, Kestrel 5400, HOBO weather station	Overall catchment area
Outcomes measured for subset of population				
Personalised heat exposure	Baseline, monthly	Occupation, sun exposure, illness history, daily routine	Structured survey tool (adapted from HotHaps)‡ and Temp-U	Indexed adults randomised for sub-group
Physiological strain markers	Continuous throughout summers	Heart rate, sleep cycles, VO₂¶ max	Fitbit Inspire 3	Indexed adults randomised for sub-group

* WHOQOL-BREF: World Health Organization Quality of Life - Brief

† Cold and Heat Exposure Questionnaire

‡ High Occupational Temperature Health and Productivity Suppression

§ Universal Thermal Climate Index

¶ Volume of Oxygen

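### The co-primary quality-of-life outcome is sized as a between-arm difference in level but analysed as a year-1 to year-2 change, which removes any benefit already present in year 1

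*Protocol article*

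**What the plan says.** Table 3 schedules the WHOQOL-BREF at "Mid of April, July and December for two consecutive years", which makes six visits, three of them in year 1. Under Study design the trial runs from 1 January 2026 to 31 December 2027.

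The Sample size section sizes quality of life "to detect a difference of 4 points in quality of life score, assuming an ICC of 0.015", from a mean of 68 (SD 18.0), with 11 clusters per arm and 60 households per cluster. It calls this cross-sectional calculation conservative because "the planned repeated-measures mixed-effects analysis increases precision by combining information across visits". It places the outcome second in a fixed sequence: "quality of life will be tested at 0.05 only if the first test is significant".

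The Statistical analysis section describes repeated-measures mixed models with assignment and season as fixed effects, adjusted for baseline values where available. It names no arm-by-year term.

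The Primary outcome analysis section, which should state the test, says that "the mean increase from year 1 to year 2 would be compared three times a year". It adds that summer and winter means will be examined separately, and that results are adjusted mean differences with 95% CIs.

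**The concern.** A between-arm difference in level, averaged over visits, asks whether people in intervention clusters have better quality of life. A between-arm difference in the year-1 to year-2 increase asks whether the gap between arms widened in the second year. The two agree only if there was no gap in year 1.

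No part of the article makes year 1 a control year or dates delivery. The one indirect clue, under Environmental data collection, is a drone survey before intervention and then once yearly, which suggests delivery during year 1. If so, some or all of the benefit would already be in the year-1 scores and would be subtracted from the co-primary result. An effective bundle could then fail its second co-primary test.

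The fixed sequence also needs one quality-of-life test at 0.05. The stated analysis gives a change for each of three calendar points and does not say which of them, or what combination, is that test.

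**Working it through.** **Inputs from the article:** difference 4 points, SD 18 (variance 324), ICC 0.015, k = 11 clusters per arm, m = 60 index adults per cluster, two-sided 0.05, 80% power. Two-sided testing is stated for heat-related illness and taken to apply to quality of life.

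**Assumed, not in the article:** within-person correlation r from 0.3 to 0.7, and cluster autocorrelation c from 0.8 to 1.0.

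**1. Reproduce the planned figure.** Under the normal approximation, n per arm = 2 × 324 × (1.960 + 0.842)² / 4² = 317.9. Then m = n(1 − ICC)/(k − n × ICC) = 317.9 × 0.985/(11 − 4.77) = 50.2, which is not 60. With t quantiles on 20 df, n = 2 × 324 × (2.086 + 0.860)² / 16 ≈ 351.5, and m = 351.5 × 0.985/(11 − 5.27) = 60.4. So 60 reproduces with a small-cluster correction, and the formula is for a difference in **level at one visit**. Check: SE = √[2 × 324 × (1 + 59 × 0.015)/660] = 1.36, giving 79.9% power at 4 points.

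**2. Expected value of each contrast.** Let the between-arm effect be d1 in year 1 and d2 in year 2. Each seasonal change estimates d2 − d1. The six-visit mean estimates (d1 + d2)/2. With d1 = d2 = 4 the change is 4 − 4 = 0.

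**3. Standard errors.** Between-cluster variance B = 0.015 × 324 = 4.86; within-cluster variance W = 324 − 4.86 = 319.14.
- One seasonal change: SE² = 2 × [2B(1 − c)/11 + 2W(1 − r)/660]. SE runs from 0.76 (r = 0.7, c = 1.0) to 1.31 (r = 0.3, c = 0.8).
- Six-visit mean level: SE² = 2 × [B(1 + 5c)/(6 × 11) + W(1 + 5r)/(6 × 660)]. SE runs from 1.07 (r = 0.3, c = 0.8) to 1.27 (r = 0.7, c = 1.0).

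**4. Power, t on 20 df, over the assumed correlations.**

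| Effect in year 1, year 2 | Each year-on-year change | Mean level, six visits | Mean level, year 2 only |
|---|---|---|---|
| 4, 4 | 5% | 85–94% | 84–92% |
| 3, 4 | 11–24% | 75–88% | 84–92% |
| 2, 4 | 31–70% | 61–76% | 84–92% |
| 0, 4 | 83–99.9% | 32–43% | 84–92% |

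If the effect is absent only at the first April visit and is 4 points afterwards, the April change carries the effect. The July and December changes each have expectation 0 and reject 5% of the time. The mean of the five later visits has 85–94% power.

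The last row of the table matters for the fix: pooling all six visits is itself poor if year 1 is wholly pre-effect. The contrast must be tied to post-intervention visits, so the delivery date has to be stated.

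**5. Multiplicity, conditional.** If the three changes were each tested at 0.05 and any one counted as success, the chance of at least one false quality-of-life result would be 1 − 0.95³ = 0.143. This applies where heat-related illness is truly improved, the gate is passed and quality of life is not improved.

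**The case against.** The strongest defence is that the loss of power is conditional. Each dwelling must be surveyed, assessed for structural safety, consented and cost-shared before work starts, and mid-April 2026 is only three and a half months after the planned start. If delivery took most of year 1, the change would approach a valid difference-in-differences, with 83–99.9% power. That stands: 5% is one end of a range, not a prediction. But the article nowhere says that year 1 precedes the effect.

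Second, the model itself is not in conflict. The 60 households come from a cross-sectional formula, the mixed model is cited only to call that figure conservative, and year-on-year changes can be estimated inside such a model. That also stands: the conflict is over the contrast.

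Third, the exact gated contrast is often left to an analysis plan, which is not shown. Here, however, the article does state a contrast, and it is not the one powered.

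A reader might also infer three stronger points, which the article does not support:
- *That the heat-illness analysis treats year 1 as on-intervention, so the two co-primary analyses cannot both be right.* The text says only that "person-weeks at risk will be used as the denominator". It gives no start date or years, and a roll-out through year 1 could accommodate both.
- *That family-wise error is 14%.* When both nulls are true the gate holds it at 5% or less. The any-one-of-three rule is never stated, and the phrase about three comparisons a year may only restate the visit schedule.
- *That seasons are compared with each other instead of arms.* The mention of adjusted mean differences fits arms compared within season.

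**Conclusion.** The concern holds as a conflict of contrasts on a co-primary outcome. The Sample size section powers a difference in level combined across visits, the Primary outcome analysis section specifies a year-on-year change, and no single contrast is assigned to the gated test. Confidence in that conflict is high, because it rests on stated text.

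The size of the loss depends on how much of the effect is present in year 1, which cannot be known while delivery is undated. Power per change runs from 5% with a constant effect to 83–99.9% with none in year 1. The ranges rest on the assumed correlations, a 4-point effect in year 2 and 60 analysed adults per cluster; they include no gain from baseline adjustment. The 14% figure is an upper value under a success rule that the article does not state, and only once the gate is passed.

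This should be settled before analysis, because a fully effective intervention could yield a null co-primary result.

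**What to change.** 1. State when the intervention starts relative to the April year-1 visit, so that it is clear which visits are post-intervention.
2. Replace the year-on-year sentence with one primary contrast for the gated 0.05 test: the between-arm adjusted mean difference in WHOQOL-BREF, averaged over all post-intervention visits. Estimate it from one linear mixed model with arm, visit (season by year), pre-intervention quality of life as a covariate, and random effects for cluster and participant.
3. Make the season-specific and year-on-year contrasts secondary.
4. Bring the Sample size, Statistical analysis and Primary outcome analysis sections into line with that contrast.

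The cost is protocol wording. All six visits are already scheduled, and Box 1 lists a quality-of-life section in the data collection tool, so no extra visit appears to be needed.
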